### Interventions

#### Exercise groups

Participants randomized to the exercise intervention groups will engage in a 12-week exercise program consisting of either intermittent exercise (IE) or graded exercise (GE). The exercise sessions will be group-based and conducted at the Southern Cross University Health Clinic, three times per week. All sessions will be supervised by an accredited Exercise Physiologist (AEP) and post-graduate clinical exercise physiology students. Each exercise session will consist of a 5 minute gentle warm up of unloaded cycling, followed by initially a 10 to 15 minute block of either steady state exercise (GE) or intermittent exercise (IE) at an intensity pre-determined from the baseline VO_2peak_ cycle test for each participant. Depending upon the symptom limits of the exercise, the duration of the exercise block can be gradually increased for each participant as tolerated to either a steady state (constant effort) low-moderate intensity cycling period, (50% VO_2peak_, RPE 3 [0–10 Borg Scale]) initially for 10 minutes (GE group) OR an intermittent exercise block of 1 minute of moderate intensity cycling (60% VO_2peak_, RPE 4–5) alternated with 1 minute of unloaded or very low intensity/unloaded cycling (20-30% VO_2peak_, RPE 1–2), totalling 20 minutes. A cool down of 5 minutes unloaded cycling plus stretching of main muscle groups for both groups is also included in the exercise session.

During the 12 weeks of training, we aim to progress the duration of GE towards 20 min, as tolerated by the participant, and to progress the IE participants towards intervals of 2–3 min of moderate intensity cycling, alternated with 1 minute intervals of low intensity cycling, totalling 25–30 min duration. Resting heart rate, heart rate variability (standard deviation of the normal to normal R-R intervals and the root mean square of differences of successive R-R intervals), resting blood pressure, RPE, (0–10 Borg Scale) and fatigue levels will be recorded prior to, and after, each exercise session. Participants will be asked to record any changes, such as elevated or depressed mood, changes to sleep patterns or general well-being, that they perceive to have occurred during their participation in the exercise training.

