### Sample size and power calculation

A previous exercise intervention study provided VO_2peak_ data from a CFS sedentary, age-matched cohort (16.2±1.3 yr) [18]. This data has been used to compute statistical power *a priori* using the non-commercial statistical power analysis program G*Power. The control group is expected to experience no change in the aerobic capacity after 12-weeks while the intervention groups are expected to increase this measure following the exercise interventions. Setting an alpha level of 0.05, approximately 75 participants (25 per group) will provide 82% power to detect a statistically significant difference between groups. Recruitment will be inflated to 90 participants to enable a 20% participant attrition rate.

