### Participants

The inclusion criteria for the study are a medical diagnosis of CFS from the participant’s medical practitioner, according to CDC criteria; an age range of 16 to 60 yr; no diagnosed cardiorespiratory, endocrine, metabolic condition or current musculoskeletal injury that would make exercise participation hazardous; the ability to communicate in English; provision of informed consent; willingness to participate in three exercise sessions per week. Participants will be recruited from the local community through advertisements at the Southern Cross University campus and Health Clinic, local medical clinics and hospitals, local newspapers, television and radio media. Participants will be randomized *via* computer-generated randomly permuted blocks stratified by gender and age (< 40 years; > 40 years) into the intervention groups and control group. A university employee not involved in exercise testing or delivery of the intervention will prepare the randomization assignments. Group assignment will be delivered to participants in sealed envelopes upon the completion of baseline testing. Participants who have been randomized into the control group will be offered a supervised 12-week exercise program upon completion of the study.

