### Statistical analyses

Primary analysis will be via intention-to-treat with all patients included regardless of dropout or level of adherence. Missing data will be imputed according to the maximum likelihood expectation algorithm via the Statistical Package for the Social Sciences (SPSS© Version 19.0). Physiological and exercise test data will be presented as the mean ± standard deviation, with confidence intervals used to express group differences. Changes between groups and the time effect for each group will be determined by repeated measures analysis of variance with a Bonferroni adjustment for significant differences between groups. Cohen’s Effect sizes and 90% confidence intervals will be calculated, to utilise a magnitude-based approach to inferences [41], with the following descriptors applied: (1) Effect size thresholds: <0.2 trivial, <0.6 small, <1.2 moderate, <2.0 large, <4.0 very large, >4.0 extremely large, and (2) Thresholds for assigning qualitative terms to chances of substantial effects: <0.5%, almost certainly not; <5.0%, very unlikely; <25%, unlikely; <75%, possible; >75%, likely; >95%, very likely; >99.5%, almost certain. An effect is unclear if its confidence interval includes both substantial increases and decreases [41]. A p value of < 0.05 will be considered indicative of statistical significance; clinical significance will be interpreted in light of the meaningfulness and magnitude of the adaptations observed. Data from linear pain scales will be recorded pre- and post-study, and reported as frequencies of scores between 0 and 10. Data will then be analysed using ANOVA (group and time effects). Data from wellness indices will be recorded pre and post, combined into domains and a representative total score from the time points analysed using an ANOVA. Data (non parametric) from the Fatigue scales, also measured at time points, will be collated and analysed using a Kruskall-Wallis test.

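### Exercise is delivered in group sessions in two of three arms, but the planned tests and the 82% power make no allowance for correlation within session groups; if it is positive, both are optimistic, mainly for IE v GE

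*Protocol article*

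**What the plan says.** All references are to the protocol article.

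- **Participants:** the unit of randomisation is the individual. "Participants will be randomized *via* computer-generated randomly permuted blocks stratified by gender and age".
- **Exercise groups:** both exercise arms train together. "The exercise sessions will be group-based and conducted at the Southern Cross University Health Clinic, three times per week". An exercise physiologist and postgraduate students supervise every session. Intensity is set for each participant from the baseline test, and duration is progressed according to tolerance.
- **Control group:** participants follow their practitioner's advice and attend no sessions during the trial.
- **Sample size and power calculation:** "approximately 75 participants (25 per group) will provide 82% power to detect a statistically significant difference between groups". Alpha is 0.05 and the software is G*Power. The expected pattern is no change in controls and an increase in both exercise arms. No effect size, standard deviation, test, ICC or design effect is given.
- **Statistical analyses:** "Changes between groups and the time effect for each group will be determined by repeated measures analysis of variance", with a Bonferroni correction for between-group comparisons. Pain and wellness go to ANOVA, and the fatigue scales to a Kruskal-Wallis test. No term for session group or supervisor appears.

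**The concern.** This is a partially nested design: participants are grouped in two arms and ungrouped in the third. Members of one session group share supervisors, companions and timing for 12 weeks, so their Week 13 outcomes may resemble each other more than those of participants in different groups. Repeated measures ANOVA, ANOVA and Kruskal-Wallis all treat participants as independent. A positive within-group correlation would make their standard errors too small.

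The second hypothesis is the most exposed, because it compares IE with GE and both arms are grouped. A difference between a handful of session groups could then be read as a difference between exercise types. In exercise-v-control comparisons only one side is grouped, so the effect is smaller. Self-reported exertion, fatigue and pain, which the Design section lists as primary, are more open to shared influences than an individually measured VO2peak.

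**Working it through.** **Inputs from the protocol.** 25 per arm, 75 in total, alpha 0.05, 82% power; individual randomisation; group delivery in IE and GE only; Bonferroni correction.

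**Assumed, because the protocol does not give them.** Two-sided tests; session groups of m = 5, which makes 25/5 = 5 groups per arm; fixed group membership; ICC 0.02 to 0.10, with 0 as reference.

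**Step 1: the stated 82%.** It cannot be reproduced, because the effect size, standard deviation and test are missing. It can be back-solved. For a one-way ANOVA with three groups and N = 75, 82% power needs f = 0.375. If both exercise arms shift by d and controls do not, the between-group variance is (2/9)d², so d = 0.375/√(2/9) = 0.80. A two-sided t-test of one exercise arm v control then has noncentrality 0.795 × √(25/2) = 2.81 on 48 degrees of freedom, and power 79% at an unadjusted 5%. Independence in this calculation is inferred; the protocol does not name the model.

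**Step 2: standard-error ratios.** The design effect is DE = 1 + (m − 1) × ICC. The true standard error divided by the one the planned test uses is

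- IE v GE (both arms grouped): r = √DE
- exercise v control (one arm grouped): r = √((1 + DE)/2)

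**Step 3: false-positive rate.** The actual rate is 2 × [1 − Φ(z/r)], with z = 1.96 at 5% and z = 2.394 at 0.05/3 = 1.67%, the Bonferroni level for three pairs.

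| m = 5 | DE | r, v control | r, IE v GE | 5% test: v control | 5% test: IE v GE | 1.67% test: v control | 1.67% test: IE v GE |
|---|---|---|---|---|---|---|---|
| ICC 0 | 1.00 | 1.000 | 1.000 | 5.0% | 5.0% | 1.7% | 1.7% |
| ICC 0.02 | 1.08 | 1.020 | 1.039 | 5.5% | 5.9% | 1.9% | 2.1% |
| ICC 0.05 | 1.20 | 1.049 | 1.095 | 6.2% | 7.4% | 2.2% | 2.9% |
| ICC 0.10 | 1.40 | 1.095 | 1.183 | 7.4% | 9.8% | 2.9% | 4.3% |

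Larger groups raise these. At ICC 0.05, IE v GE is 10.4% (m = 10) and 13.3% (m = 15) for the unadjusted test, and 4.7% and 6.6% at the Bonferroni level.

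**Step 4: power, variance effect only.** Divide the noncentrality 2.81 by r and keep 48 degrees of freedom. At m = 5, power v control at an unadjusted 5% is 79% (ICC 0), 77% (0.02), 75% (0.05) and 71% (0.10).

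**Step 5: the separate cost of few groups.** A test that respects session groups has few degrees of freedom: 2 × (5 − 1) = 8 for IE v GE, and about 14 by Satterthwaite v control at ICC 0. At m = 5 and ICC 0, power is already 74% v control and 69% for an IE v GE difference of the same size. At ICC 0.05 it is 69% and 62%. The step from 79% to 74% or 69% is the price of the model, not of correlation.

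**The case against.** The strongest reply is that the consequence is hypothetical. The protocol gives no ICC, session size, number of groups or statement that participants stay in one group. Prescription is individual, VO2peak is measured in an individual test, and the 82% concerns VO2peak, the outcome least likely to carry a group effect. Attendance across mixed sessions would weaken any correlation and would also make a single nested random effect the wrong model. This stands: the point has to be conditional.

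Three stronger readings are tempting, and the document does not support them.

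- A reader might infer that the standard errors are too small and the 82% overstated as matters of fact. Nothing in the document shows a positive ICC. At ICC 0.01 and groups of 5, the IE v GE error rate is only 5.5%. The 82% also cannot be checked under independence.
- A reader might take the unadjusted rates as those of the planned comparisons. The plan applies Bonferroni. At that level, groups of 10 and ICC 0.05 give 4.7% against 1.67% for IE v GE, an excess of about 3 points rather than 5.
- A reader might attribute the whole fall in power under a valid test to correlation. Part of it is the degrees-of-freedom cost in Step 5, which is present at ICC 0.

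It can also be said that this is a condensed article on a pilot trial, and that random effects belong in a fuller document. That is fair for model details. But the article does name its tests and commit to a power figure, and neither allows for group delivery, which the same article describes. That part of the objection does not remove the point.

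**Conclusion.** The point holds conditionally. The design is partially nested, and the tests as written treat participants as independent. Any positive correlation within session groups makes them too liberal and the 82% optimistic, more for IE v GE than for exercise v control.

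Under the assumed groups of 5 and ICC 0.02 to 0.10, the effect is modest v control: about 0.2 to 1.2 points of error rate at the Bonferroni level and 2 to 8 points of power. It is larger for IE v GE, where the Bonferroni-level error rate can reach about two and a half times nominal (4.3/1.67 = 2.6). The figures assume stable groups and an ICC that the document does not supply. With no correlation there is no effect. This is a worthwhile, inexpensive improvement that protects the IE v GE conclusion; it does not show that the planned analysis is invalid.

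**What to change.** 1. **Data collection:** record each participant's session group and supervisor, including any change during the 12 weeks. Without this, clustering can be neither examined nor allowed for later.
2. **Statistical analyses:** for IE v GE and exercise v control, add a partially nested mixed model with a random session-group effect in the exercise arms, each control as a singleton, and small-sample degrees of freedom (Satterthwaite or Kenward-Roger). Pre-specify it at least as a sensitivity analysis, and require it to support any claimed IE v GE difference. If membership turns out to be mixed, say how group is assigned for this model.
3. **Sample size and power calculation:** state that the 82% assumes independent outcomes, and give power over a range of ICC at the planned session-group size.

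**Cost:** a small addition to data collection (session group, with supervisor), some analysis wording, and a less favourable stated power. Intervals will be wider and power lower because there are few session groups, mainly for IE v GE. No extra participants and no change to how sessions are delivered are needed.

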#### Control group

Participants randomized to the control group will be asked to follow the advice of their medical practitioner (rest, maintaining activity for daily activities, [ADL]). Control group participants will be advised not to engage in any other physical activity, and will be offered a similar 12-week exercise program after completion of the current study. All study participants will be asked to complete an ADL diary to control for normal daily movements.

### Outcome measures

All outcome measures will be collected at baseline (Week 0) and after the exercise interventions (Week 13). Trained research personnel blinded to the randomization procedures will conduct the initial participant screenings and baseline assessments, which include a full medical history, resting heart rate, resting blood pressure and anthropometry (height; weight; BMI; waist, hip and limb girths), fatigue severity and wellness questionnaires. The project outcome measures consist of a full cell count; lymphocyte receptor flow cytometric assays; incremental cycling test (VO_2peak,_ anaerobic threshold); spirometry; Personal Well Being Index [33] and Fatigue Severity Scale [34].

#### Measures of immune function

The baseline and post-study full blood count with leukocyte differential will be performed by Northern Pathology at Lismore Base Hospital. Blood samples will be de-identified and numerically coded. Ten mL of blood will also be drawn to provide for flow cytometric assays of CD3^+^CD4^+^CD^+^135 (T helper), CD3^+^CD8^+^ (cytotoxic effector) lymphocytes, CD45^+^ (HLA marker), CD3^+^CD19^+^ (B cells) and CD56^+^CD16^+^ Natural Killer (NK) cells. The absolute concentration of these lymphocyte subsets will be measured by flow cytometer (FACSCanto ll, BD Biosciences, Australia) using the BD Multitest 6-colour direct immunofluorescence TBNK reagent and BD Trucount tubes (BD Biosciences, Australia) and FACSDiva v4.1 software (BD Biosciences, Australia).

The method for stimulating and measuring CD4^+^CD25^+^CD134^+^ expression in whole blood samples is described by Zaunders et al., (2009) [35]. Briefly, sodium heparin anti-coagulated whole blood (0.5 mL) will be mixed with 0.5 mL RPMI-1640 (Sigma-Aldrich, Australia), and will be stimulated by 5 μg/mL phytohemagglutinin (PHA) (Sigma-Aldrich, Australia) for 48 hr at 37°C in a 5% CO_2_ incubator. After culture, 100 μL of sample will be stained with the following conjugated fluorochromes for 15 min at room temperature (CD3-FITC; CD4-Per-CP; CD25-APC; CD134-PE, BD Biosciences, Australia), followed by washing in PBS (1 mL), resuspension in 0.5 mL of 0.5% paraformaldehyde (Sigma-Aldrich, Australia) and then multi-parameter flow cytometric analysis.

In a separate assay, both CD3^+^CD8^+^ and NK lymphocytes can be stimulated in an anti-coagulated whole blood sample (0.5 mL blood and 0.5 mL RPMI-1640) by using phorbol-12-myristate-13-acetate (PMA) (2.5 μg/mL) and ionomycin (0.5 μg/mL). The activation of CD3^+^CD8^+^ will be assessed through the co-expression of CD38 in response PMA and ionomycin following a 6 hr incubation at 37°C in a 5% CO_2_ incubator. The cytotoxic response of CD3^+^CD8^+^ will be measured with the expression of LAMP-1 (CD107a) and LAMP-2 (107b) as positive markers of degranulation (perforin-granzyme mediated killing) plus the concurrent intracellular production of IFN-γ [36]. NK lymphocytes will be also be stimulated by PMA and ionomycin for 6 hr to measure the expression of CD107a as an indicator of cytotoxic activity and degranulation [37]. After stimulation of CD3^+^CD8^+^ and NK cells, washing of the cells in PBS and resuspension in paraformaldehyde, receptors can be measured as follows: CD3-Per-CP; CD8-APC-H7; CD38-PE-Cy7; CD107a-APC; CD107b-FITC; CD16-PE; CD56-PE (BD Biosciences, Australia). In each experiment, a negative control (no PHA or PMA/ionomycin) will be included to control for spontaneous receptor expression or cytokine production.

#### Measures of aerobic capacity

Each participant will undergo an incremental test to volitional exhaustion on a cycle ergometer (Lode Excalibur, Holland). Peak *V*O_2_ (mL.kg^-1^.min^-1^), *V*CO_2_, ventilation (*V*_E_ BTPS L min^-1^), ventilatory equivalents (*V*E/*V*O_2_, *V*E/*V*CO_2_) and respiratory exchange ratio (RER) will be measured using open circuit spirometry (AEI, Australia), and recorded every 15 s, with peak values determined from the average of the two highest values attained over two collection periods during the exercise test. The criteria for attaining *V*O_2peak_ are when (1) *V*O_2_ increases by < 0.15 L. min^-1^ despite an increase in power, (2) heart rate is within ten beats of age-predicted maximum, (3) when RER ≥ 1.15 and (4) when RPE ≥ 8 on the 0–10 Borg Scale. However we also accept that symptom limits (fatigue) may stop the exercise test before these criteria are reached. Throughout each incremental exercise test, heart rate and rhythm will be monitored from bipolar leads in the CM5 position; blood pressure will be monitored every 2 min with standard auscultation; power (W) will be recorded every 60 s (Lode Excalibur, Groningen, Holland). Anaerobic threshold will be determined from incremental test results using the V slope method [38], a computerized regression analysis of the slopes of the CO_2_ uptake (VCO_2_) vs. O_2_ uptake (VO_2_) plot, which detects the beginning of the excess CO_2_ output generated from the buffering of [H^+^], relative to oxygen uptake.

#### Fatigue and muscle pain

RPE and fatigue will be recorded at rest and during the incremental exercise test. Participants will be asked to complete a linear pain scale (0 – 10) to indicate if they have any muscle or joint stiffness or soreness prior to the exercise test, immediately post-exercise and also 24 hours post-exercise test. RPE and pain scales will also be completed at every training session to carefully monitor symptoms. The Fatigue Severity Scale [34] and the Chalder Fatigue Scale [39], both CFS-specific, will be administered pre- and post-study to assess the severity and nature of the fatigue, mental and physical.

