**Methods/design:**

90 patients aged between 16 to 60 years, who meet the diagnostic criteria for CFS and have been diagnosed by their medical practitioner, will be randomly recruited into groups consisting of Intermittent exercise, Graded exercise and usual care (Control). The outcomes will be measured pre-study (Week 0) and post-study (Week 13). Primary outcomes are VO_2peak_, anaerobic threshold, peak power, levels of fatigue, immune cell (CD3^+^CD4^+^, CD3^+^CD8^+^, CD19^+^, CD 16^+^CD56^+^) concentrations and activation. Secondary outcomes include onset of secondary CFS symptoms (e.g. fever, swollen lymph nodes), wellness, mood and sleep patterns. Primary analysis will be based on intention to treat using logistic regression models to compare treatments. Quantitative data will be analysed using repeated measures ANOVA with a linear model, and Cohen’s effect size. Qualitative data such as participants’ responses (e.g. changes in mood and other reactions) following the exercise modalities will be read and sections demarcated. A code will be applied to each segment. A prevalence of codes will be considered thematically.

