## Background

Currently there is no clear aetiology associated with Chronic Fatigue Syndrome (also known as Myalgic Encephalitis). The syndrome is characterised by persistent, disabling and/or recurring fatigue, not alleviated by rest, and with other symptoms such as muscle weakness and pain, swollen lymph nodes and fever, poor concentration and reduced quality of life [1,2]. A medical diagnosis is made when three of the following criteria from the Centre for Disease Control and Prevention’s modified case definition of CFS, have been met [3]:

(1) The individual has had severe chronic fatigue for 6 or more consecutive months and the fatigue is not due to ongoing exertion or other medical conditions associated with fatigue (these other conditions need to be ruled out by a doctor after diagnostic tests have been conducted).

(2) The fatigue significantly interferes with daily activities and work.

(3) The individual concurrently has 4 or more of the following 8 symptoms: post-exertion malaise lasting more than 24 hours; unrefreshing sleep; significant impairment of short-term memory or concentration; muscle pain; pain in the joints without swelling or redness; headaches of a new type, pattern, or severity; tender lymph nodes in the neck or armpit; a sore throat that is frequent or recurring.

These symptoms should have persisted or recurred during six or more consecutive months of illness and they cannot have pre-dated the fatigue.

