Strategies to manage CFS include pharmacology, physical activity where appropriate (for example graded exercise (GE) and pacing), and psychological approaches such as cognitive behavioural therapy (CBT) which seek to modify behaviour, beliefs and coping strategies. [17-20]. Current best practice for the physical training of CFS patients involves GE sessions where the patient exercises at a well-tolerated constant rate or load (steady state), and the duration of the exercise session is gradually increased over time [2,18-20]. CBT is usually combined with exercise management [18,20].

Evidence of the efficacy of GE, CBT, pacing and other prescriptions of physical activity has been mixed. Some CFS patients still report symptom exacerbation and muscle pain with GE, and consequently are less likely to be physically active [21,22]. Yet other studies have reported that aerobic and resistance exercise improves aerobic capacity and strength [13], fatigue [17], profile of mood states and inflammatory cytokines [14,17,21,23-26].

Intermittent training, where intervals of exercise are alternated with intervals of rest or very low intensity exercise, has been used with cardiac [27], pulmonary [28,29], cancer [30] and older clients who are very deconditioned [31]. Clapp et al. (1999) reported that an acute session of intermittent exercise for 30 minutes did not exacerbate CFS symptoms immediately post-exercise, or for up to 7 days post exercise [32]. In CFS patients, intermittent training may increase exercise tolerance by decreasing perceived exertion, and delaying the onset of fatigue and muscle pain, whilst still providing the same total amount of physical activity as GE. Patients may find it easier to adhere to an intermittent exercise programme if their symptoms are not exacerbated, and therefore may improve their health.

Study hypotheses and aims: the primary aim of the trial is to investigate the efficacy of 12 weeks of intermittent or graded exercise on aerobic capacity, fatigue, immune function and wellness in CFS patients compared to standard care (typically rest, pharmacology and advice about physical activity). We hypothesise that:

1) Both exercise interventions will improve exercise tolerance, aerobic capacity and wellness compared to the control condition, and

2) IE will result in greater exercise tolerance, less fatigue and other symptoms, improved immune function and better exercise adherence compared to GE.

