## Methods

### Design

This study is a randomised controlled trial that will compare the outcomes of a 12-week intermittent cycling exercise program to a graded exercise cycling program and standard care (rest and lifestyle advice). The primary outcomes of the study are aerobic capacity (VO_2peak_), perceived exertion, fatigue, muscle pain, immune cell counts, lymphocyte (CD4^+^, CD8^+^, CD19^+^, CD16^+^56^+^) concentrations and function. Secondary outcomes are wellness indices and physiological adaptations to exercise (changes in heart rate, heart rate variability, blood pressure, body composition, anaerobic threshold) and measures of presence, severity and type of fatigue (mental and physical). Southern Cross University Research Ethics Committee has approved all study procedures (HREC ECN-13-066).

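### The outcome named muscle pain is recorded on a scale that also covers joint symptoms, so a result on it, positive or null, cannot be attributed to muscle pain

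*Protocol article*

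**What the plan says.** Five places in the protocol article bear on this.

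- **Design** gives muscle pain primary status: "The primary outcomes of the study are aerobic capacity (VO_2peak_), perceived exertion, fatigue, muscle pain, immune cell counts".
- **Abstract, Methods/design** gives a different list that does not contain muscle pain: "Primary outcomes are VO_2peak_, anaerobic threshold, peak power, levels of fatigue, immune cell".
- **Fatigue and muscle pain** describes the instrument, a "linear pain scale (0 – 10) to indicate if they have any muscle or joint stiffness or soreness". It is completed before the incremental test, immediately after it and 24 hours later. Pain scales are also completed at every training session.
- **Statistical analyses** states how it is handled: "Data from linear pain scales will be recorded pre- and post-study, and reported as frequencies of scores between 0 and 10". An ANOVA for group and time effects follows. Nothing separates muscle from joint.
- **Background** lists the two complaints as distinct items in the case definition: "muscle pain; pain in the joints without swelling or redness". The rationale for intermittent training is specific to muscle. It speaks of "delaying the onset of fatigue and muscle pain" and proposes no effect on joints.

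**The concern.** The outcome is named for one symptom and the scale is worded for two. Four of eight symptoms are needed for the diagnosis, and muscle pain and joint pain are separate entries among the eight. An eligible participant can therefore have either without the other. Someone with stiff joints and no muscle pain could properly give a positive answer on this scale, and that answer would be analysed as muscle pain.

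What is at stake is interpretation. The trial wants to know whether intermittent cycling provokes less muscle pain than steady graded cycling. On a combined score, a difference could come from muscle, joint or both. A null result could mean no effect on muscle, or an effect on muscle masked by joint symptoms. The two sites cannot be separated once the data have been collected.

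**Working it through.** **Step 1. Set the passages side by side.** Named outcome: muscle pain (Design). Recorded quantity: stiffness or soreness of muscle or joint, 0–10 (Fatigue and muscle pain). Analysed quantity: the same score, not split (Statistical analyses). Status of the two symptoms: separate (Background). The mismatch follows from the text alone.

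**Step 2. Look for a stated figure.** There is none for pain. The only power statement, "Setting an alpha level of 0.05, approximately 75 participants (25 per group) will provide 82% power", is based on VO2peak. It gives no effect size or SD, and this point does not alter it. The article also gives no prevalence of joint symptoms, no muscle–joint correlation, no expected joint response, and no rule for combining the sites into one answer. Every number below is therefore an assumption, varied to show direction.

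**Step 3. Combined score as a weighted average.** Let the score be S = (1 − w)·muscle + w·joint, with equal SDs and correlation r. With standardised effects d_M on muscle and d_J on joint:

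- SD factor = √[(1 − w)² + w² + 2w(1 − w)r]
- d_S = [(1 − w)·d_M + w·d_J] / SD factor

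Take d_M = 0.8, w = 0.25 or 0.5, and r = 0.3 or 0.7. Use 25 per arm and a two-sided t-test at 0.05. A pure muscle scale then has 79% power.

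Worked example: for w = 0.5, r = 0.7, d_J = 0, the SD factor is √(0.25 + 0.25 + 0.35) = 0.922, and d_S = 0.40/0.922 = 0.43.

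| Assumed joint effect d_J | d_S across w and r | Power |
|---|---|---|
| 0 | 0.43 to 0.70 | 32% to 68% |
| 0.4 | 0.65 to 0.82 | 62% to 81% |
| 0.8 | 0.85 to 0.99 | 84% to 93% |
| 1.2 | 0.96 to 1.24 | 91% to 99% |

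Setting d_S = 0.8 gives the break-even joint effect, d_J = 0.8·(SD factor − (1 − w))/w. This is 0.35 (w = 0.25, r = 0.3), 0.61 (0.25, 0.7), 0.49 (0.5, 0.3) and 0.68 (0.5, 0.7). Below that value the combined score understates the muscle effect, and above it the score overstates it.

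**Step 4. Combined score as the worse of the two sites.** This is a simulation with these assumptions: pain, when present, has mean 5 and SD 2, cut at 0 and 10; correlation is 0.3; muscle pain is present in 80% and joint pain independently in 30%, 50% or 70%; treatment lowers muscle pain by 1 point. The entries are the mean reduction in the combined score as a share of the mean reduction in the muscle score.

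| Change in joint pain | Joint pain 30% | 50% | 70% |
|---|---|---|---|
| none | 83% | 71% | about 60% |
| falls 0.5 | 96% | 93% | 90% |
| falls 1 | 108% | 113% | 118% |
| rises 0.5 | 68% | 47% | 26% |

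Under the same prevalences, the share with joint pain but no muscle pain is 0.2 × 0.3 = 6%, 0.2 × 0.5 = 10% and 0.2 × 0.7 = 14%.

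Both models agree. The score falls short if joints respond clearly less than muscle and overshoots if they respond as much or more.

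**The case against.** **Dilution is not established.** A reader might infer that joint symptoms dilute a real effect on muscle pain. The article does not support that. Dilution appears only when the joint response is assumed to be nil, adverse or clearly smaller than the muscle response, and no passage gives that response. This objection stands in full. Similarly, an example in which muscle pain falls and the score stays put needs a worst-site rating rule, and the article contains none.

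**The form may already have two marks.** The article speaks of a pain scale in one place and of pain scales in others, and it is condensed. The plurals may reflect only the repeated readings. Form layout is reasonably left to a fuller document. However, the article does state what the scale asks about and how it is analysed, and neither statement distinguishes the sites. The mismatch stands on what is written.

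**Primary status is uncertain.** Design includes muscle pain in "perceived exertion, fatigue, muscle pain, immune cell counts". The Abstract does not list it, and the numbered hypotheses refer only to other symptoms. Power rests on VO2peak. This limits the weight of the point, which should not be read as showing that the trial's main endpoint is compromised. It does not remove the point, since the Methods text gives muscle pain primary status.

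**Renaming would also work.** This is correct. It removes the mismatch without a new item, but it gives up the muscle-specific question raised in the Background.

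**Conclusion.** The point holds as a mismatch between a named outcome and its measurement. The score described does not isolate muscle pain, so neither a group difference nor its absence can be attributed to it. This rests only on the article's wording.

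The size and direction of any distortion cannot be determined from the article. With assumed inputs, a true muscle effect of 0.8 SD could appear as anything from 0.43 SD (joint symptoms unresponsive) to 1.24 SD (joint response 1.2 SD). Power with 25 per arm would run from 32% to 99%, against 79% on a pure muscle scale. These figures depend on the assumed weights, correlations and joint effects and should be quoted only as a two-way range. No stated sample size or power figure changes.

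**What to change.** In Fatigue and muscle pain, collect two 0–10 ratings at each existing reading: one for stiffness or soreness of muscle, one for stiffness or soreness of joints. Worded this way, muscle stiffness stays with the muscle rating and nothing the present scale asks about is lost. In Statistical analyses, state that the muscle rating is the muscle pain outcome and that the joint rating is reported as secondary. Make the Abstract and Design agree on whether muscle pain is primary.

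If a single combined rating is kept, rename the outcome to say that it covers both sites, and state that no muscle-specific conclusion will be drawn from it.

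The cost is one extra mark per reading and one more secondary outcome on an already long list. No visit, staff or procedure is added. The change must be made before data are collected, because a combined answer cannot be split afterwards.
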